### Intervention and control group

The intervention group participate for three years (or until school entry) in EYEP. The control group receive what we refer to as ‘usual care’. This is a mix of parental and guardian care, and education and care provided by other local childcare centres or kindergartens. The usual care is determined by the choice of the child’s parent(s) without any direction; that is, there is no direct effect on the control group’s early education and care due to participation in the EYEP trial.

Nevertheless, it is possible that the control group may be affected by participation in the trial. For example, awareness of EYEP and its objectives may alter the decisions that parents of children in the control group make about their children’s early education. In addition, all children receive an annual development report which may change decisions that control group families make about their children’s needs and which services to access. Hence we plan to construct an extra quasi-experimental control group by matching trial participants with a group of children with similar background characteristics from the Longitudinal Survey of Australian Children (LSAC). By collecting some data items on outcomes for trial participants that are also collected for children in LSAC, we will be able to compare outcomes for the EYEP intervention and control groups with a control group from general population survey of children.

### Outcome measures

Data are being collected on participants in EYEP and the control group at the baseline (within 3 months of entry to the trial), at yearly intervals for three years after entry to the trial, and six months after commencing the first year of school (Prep grade).

Measures for data fields have been chosen on the basis of knowledge of international best-practice in measurement of child development. The measures have also been selected in order to enable comparisons with existing literature on child development and well-being and studies of previous trials such as Abecedarian, as well as to match with data items available for the alternative control group from the Longitudinal Survey of Australian Children. Table 
1 lists the categories of data being collected on children and parents that relate to the main hypotheses in this study and the instruments being used.

**Table 1 Tab1:** **Study measures and time points**

Study measure	Entry	Annual	School
**Hypothesis 1a) Children’s health and development outcomes**			
*Cognitive development*			
Bayley scales of infant and toddler development III (BSID)^a^	X	X	
Wechsler preschool and primary scale of intelligence (WPPSI) – Valid for ages 2.6-7.3^b^		X	X
*Language and socio-emotional development*			
Peabody Picture Vocabulary – Valid for ages 2 + ^c^		X	X
Child health questionnaire – Valid for ages 5+; Measures functional health and well-being^d^		X	X
Expressive Vocabulary Test		X	X
Longitudinal Study of Australian Children (LSAC) questions – Items on health status, injury and hospitalisation, health care access and affordability	X	X	X

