Data on background demographics and outcomes for children are being collected via standardized assessments, parent and childcare educator questionnaires, and observation and interviews. Data on parents and their outcomes – including background demographics, service usage (including childcare, counselling or social work services, usage of medical and hospital services), labour market experiences, and financial status (including income support payment history and financial stress) - is also being collected.

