### Data analysis

The data analysis will identify the impact of ‘Intention to treat’ at the level of the individual child. The analysis will compare the change in an outcome measure (at time of data collection minus at baseline) for children in the intervention group with children in the control group. Impact evaluations will be conducted on outcomes measures after the 12, 24 and 36 month data collections as well following the data collection after the commencement of the first year of schooling.

For comparisons between the randomised intervention and control groups from the trial it should be possible to estimate the program impact as the difference in mean outcomes between those groups. For continuous outcome variables this will be the difference in mean changes in the outcome between intervention and control groups. For categorical outcome variables it will be differences in the change in the proportions of children in each category between intervention and control groups. For comparisons between the EYEP intervention group and the control group from LSAC a quasi-experimental matching method (difference-in-difference) will be used. Statistical significance will be established via t-tests for individual outcomes or Hotelling T tests for groups of outcomes.

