### Economic evaluation

This analysis will quantify the benefits and costs of EYEP to society. Estimates of the net impacts of EYEP on children’s human capital development and service usage, and on outcomes for parents, will be translated into estimated monetary values, and these benefits aggregated to compare against the costs of the program, to arrive at a benefit-cost ratio for the program. The main potential benefits of the intervention are expected to derive from its effects on child health, cognitive development and interpersonal skills. Improved outcomes in these areas may yield benefits from: reduced direct cost to government such as reduced demands for health services, and reduced demand for specialized education due to better cognitive development. To assign monetary values to these benefits, we will for example collect information on the cost of health and special education services to estimate the values of reduced usage of those services. This information will then be combined with the estimated impacts of EYEP on service usage. The main costs associated with EYEP are the costs of providing the childcare and early education services; including employees’ wage costs, the cost of purchasing resources such as toys and educational materials, and maintenance costs for the program site. In undertaking the benefit-cost analysis of EYEP, it will be important to recognize what factors it may not be possible to value in monetary terms.

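### Subtracting the entry value from noisy event and service-use outcomes loses precision that adjusting for it would keep, most of all if wave changes are summed for the benefit-cost ratio

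*Protocol article*

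**What the plan says.** Table 1 of the protocol article lists, under Hypothesis 1a, child items from the Longitudinal Study of Australian Children (LSAC): "Items on health status, injury and hospitalisation, health care access and affordability". Under Hypothesis 2 it lists parent items on use of health and welfare services. Both rows are marked for entry, annual and school collections, so an entry value exists. The text after Table 1 adds parent data on "service usage (including childcare, counselling or social work services, usage of medical and hospital services".

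The Data analysis section sets one rule for all outcomes: "The analysis will compare the change in an outcome measure (at time of data collection minus at baseline". It continues: "For continuous outcome variables this will be the difference in mean changes in the outcome between intervention and control groups". Categorical outcomes are compared as "differences in the change in the proportions of children in each category between intervention and control groups". On timing it says: "Impact evaluations will be conducted on outcomes measures after the 12, 24 and 36 month data collections", with a further evaluation after school starts. No separate rule is given for events or service contacts.

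The Outcome measures section places data collection "at the baseline (within 3 months of entry to the trial), at yearly intervals for three years after entry to the trial", and again six months into the first school year. The Economic evaluation section combines unit costs with the estimated impacts on service use and has "these benefits aggregated to compare against the costs of the program". It does not name the wave or waves that supply those impacts.

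**The concern.** A change score suits a fairly stable state, such as a test score, where the entry value carries much information about the later one. Injuries, hospital stays and service contacts are sparser and vary more from year to year. When entry and follow-up are only weakly related, subtracting the entry value adds its noise to the comparison and removes little. Using the same entry value as a covariate takes out what it predicts and no more.

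This matters most for the benefit-cost ratio, a stated output of the study. If the annual impacts are added up to price use averted over the programme, the same noisy entry value is subtracted once per wave, so its error enters the sum three times. With 45 children per group and planned attrition of 20 per cent a year, there is little precision to spare.

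A second, lesser point concerns what is being estimated. The article does not define service-use impact as a quantity accumulated over follow-up. A change at one wave, taken literally, is not total use.

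**Working it through.** **1. The plan's own figure.** The article gives no design figure for event outcomes. Its only adjusted sample size, 32 per group, concerns IQ. It can be reproduced as 19 × 1.35 / 0.8 = 32.06 or as 12 × 1.35 / 0.8³ = 31.64. It has no bearing on this point.

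**2. One wave.** Assume equal standard deviations at entry and follow-up, set to 1, and entry–follow-up correlation ρ. Variance per child is 2(1 − ρ) for the change score and 1 − ρ² after adjustment. The documents give no ρ, so a range is shown.

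| ρ | Change score | Adjusted | SE ratio |
|---|---|---|---|
| 0.1 | 1.80 | 0.99 | 1.35 |
| 0.3 | 1.40 | 0.91 | 1.24 |
| 0.5 | 1.00 | 0.75 | 1.15 |
| 0.7 | 0.60 | 0.51 | 1.08 |

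The direction does not depend on equal standard deviations. With entry standard deviation k, the change score has variance 1 + k² − 2kρ. Its excess over 1 − ρ² is (k − ρ)², which is never negative. Only the size depends on k.

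**3. Three annual waves summed.** Assume the same correlation ρ between any two collections. The three-wave total has variance 3 + 6ρ and covariance 3ρ with entry. Summed changes: 3 + 6ρ + 9 − 18ρ = 12(1 − ρ). Total adjusted for entry: 3 + 6ρ − 9ρ².

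| ρ | Summed changes | Plain total | Adjusted total | SE ratio to plain | SE ratio to adjusted |
|---|---|---|---|---|---|
| 0.1 | 10.8 | 3.60 | 3.51 | 1.73 | 1.75 |
| 0.3 | 8.4 | 4.80 | 3.99 | 1.32 | 1.45 |
| 0.5 | 6.0 | 6.00 | 3.75 | 1.00 | 1.26 |
| 0.7 | 3.6 | 7.20 | 2.79 | 0.71 | 1.14 |

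The adjusted total is the more precise throughout. The plain total loses its advantage at ρ = 0.5 and is worse above that.

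**4. The same in event counts.** Assume Poisson counts with annual mean L, between-child variance in rate T and 12-month recall at each collection. Summed changes have variance 12L, and the adjusted total has 3L + 9LT/(L + T).

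- L = 0.3, T = 0: 3.6 against 0.9, variance ratio 4.0.
- L = 1, T = 0.5: 12 against 3 + 3 = 6, ratio 2.0.
- L = 2, T = 4: 24 against 6 + 12 = 18, ratio 1.33. Here the unadjusted total has 3 × 2 + 9 × 4 = 42 and is clearly worse than the summed changes.

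**5. What each quantity estimates.** Trials of 45 per group were simulated with a control rate of 0.3 events per child-year, between-child variance equal to the squared mean, and 0.27 events averted per child over three years. The 36-month change alone averaged 0.09 for a constant effect, 0.03 for a fading one and 0.15 for a growing one. The sum of the three annual changes and the plain three-year total both averaged about 0.27. Their standard errors were about 0.39 and 0.25, at ρ of about 0.23.

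**The case against.** The strongest reply is that nothing here is biased. Randomisation balances entry values in expectation, so the change score estimates the right difference at each wave. It also matches the difference-in-difference method planned for the LSAC comparison. Baseline adjustment is preferable for any outcome measured at entry, so the point is one of efficiency. All of this stands. Events are singled out because low year-to-year correlation is where the loss is greatest, and because their impacts are the ones priced.

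A reader might infer that the benefit-cost analysis ignores use in other years, or prices only one of the three programme years. The article does not support that. It estimates impact at every annual wave and aggregates benefits without limiting them to one wave. Step 5 shows that summed wave impacts recover the total in expectation, provided recall periods join up. An aggregation rule may also be given in a fuller document that is not shown.

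A reader might also infer that the baseline covers life before entry, and so means something different for a newborn than for a three-year-old. The article says only that baseline is collected within three months of entry, and it gives no recall period. If items asked about life to date, wave minus baseline would itself be the total since baseline. Unequal exposure before entry would add noise but would not bias the randomised comparison.

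Finally, nothing says that injury or hospitalisation is recorded as a count. If the items are yes/no, the Poisson figures in step 4 do not apply and a rate cannot be built from them.

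**Conclusion.** The point holds as a precision loss in a rule that the article states, not as a bias or an omission of use. For event and service-use outcomes with an entry value, the change score has a standard error about 1.08 to 1.35 times that of the adjusted comparison at one wave. If the three annual changes are summed, the factor against the adjusted total is about 1.14 to 1.75. Both ranges run from ρ = 0.7 to ρ = 0.1.

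These sizes assume equal standard deviations and, for the sum, equal correlations between all collections. Sibling clustering is left out. The fourfold variance ratio in step 4 is an extreme that needs no variation between children, which is unlikely in families selected for multiple risk factors. The gain is general only against the adjusted total; a plain total can do worse than the change score.

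That a single-wave change is not total use remains true as a matter of definition. Whether the benefit-cost analysis would in fact miss any use cannot be settled from the article.

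**What to change.** In the Data analysis section, add that for event and service-use outcomes with an entry value (injury, hospitalisation, and health, welfare and other service contacts) the groups are compared at follow-up with entry use and age at entry as covariates, instead of subtracting entry use. The test of the adjusted group difference then replaces the t-test on change for these outcomes. Keep the wave-specific results for description.

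In the Economic evaluation section, where items are recorded as counts, take as the service-use input the baseline-adjusted total or rate over non-overlapping observed follow-up, with observed time as offset. Because participation can end at school entry before three years, the 36-month and school collections may overlap; count any shared period once. Report missed waves and periods outside an item's recall as unobserved. For yes/no items, report the adjusted difference in proportions and do not present it as a number of events.

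The cost is wording, with no new data. The real work lies in stating each item's format and recall period and in handling missed waves. The latter is not trivial: 20 per cent attrition a year, if compounded, leaves 45 × 0.8³ = 23 children per group at 36 months.

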**Hypothesis 1b) Children’s academic achievement and ability**			
Woodcock Johnson NU tests – Literacy and numeracy^e^			X
Devereux Early Childhood Assessment Program (DECA) – 37 observer rated positive behaviour items (subscales are initiative, self-control and attachment)^f^	X	X	X
**Hypothesis 1c) Children’s emotional and behavioural regulation**			
Greenspan socio-emotional growth chart (SEGC) – 35 item measure of socio-emotional milestones for ages 0–42 months^g^	X		
Brief infant toddler social emotional assessment (BITSEA) – 42 item parent completed screener for social-emotional/behavioural problems for ages 12–36 months^h^	X	X	
Child behaviour checklist – Identifies behavioural problems; Valid 18+ months^i^		X	X
Alarm baby distress scale (ADDB) – Social and interactive behaviour of infant in interaction with researcher; Valid for ages 1–36 months^j^	X		

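### Hypothesis 1c: SEGC and the infant distress scale are entry-only and the behaviour checklist has no entry score, so the change rule fits none of them; use the entry scores as covariates for the checklist

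*Protocol article*

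**What the plan says.** Under Outcome measures, the article says that Table 1 "lists the categories of data being collected on children and parents that relate to the main hypotheses in this study". The table, titled "Study measures and time points", has three time columns: Entry, Annual and School. Four instruments stand under Hypothesis 1c:

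- SEGC, "35 item measure of socio-emotional milestones for ages 0–42 months": Entry only.
- Infant distress scale, "Social and interactive behaviour of infant in interaction with researcher; Valid for ages 1–36 months": Entry only.
- BITSEA, "42 item parent completed screener for social-emotional/behavioural problems for ages 12–36 months": Entry and Annual.
- Child behaviour checklist, "Identifies behavioural problems; Valid 18+ months": Annual and School, not Entry.

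The Data analysis section sets one rule for impact: "The analysis will compare the change in an outcome measure (at time of data collection minus at baseline"), intervention against control. It adds: "For continuous outcome variables this will be the difference in mean changes in the outcome between intervention and control groups". Significance is to come from t-tests, or Hotelling tests for groups of outcomes. Aims and hypotheses places the expected benefits at the end of the intervention and six months into the first school year.

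**The concern.** The schedule and the analysis rule do not fit together for this hypothesis. A scale taken only at entry has no follow-up term, so two of the four listed 1c instruments can give no effect estimate at any wave, although they sit under a heading for outcomes. The checklist has follow-up scores at the time points that the hypothesis names, but no entry score to subtract. Under the rule as stated it also drops out, or it falls back on a plain unadjusted comparison of follow-up means.

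What is at stake is precision. With 45 children per arm, entry information on emotional and behavioural functioning will be in hand for nearly every child, and the stated analysis has no way to use it for the one 1c measure that reaches the hypothesis time points.

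**Working it through.** **Inputs.** Schedule and age ranges: Table 1. Change rule: Data analysis. Entry age 0 to 3 years: Participants. Baseline within 3 months of entry: Outcome measures. 45 children per arm: Sample size and power calculations. The article gives no entry-age distribution and no correlations between scales, so those below are assumptions. There is no stated figure on this point to reproduce.

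**Step 1: schedule against the change rule.**

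| Listed 1c measure | Age range (months) | Entry | Annual | School | Change score under the rule |
|---|---|---|---|---|---|
| SEGC | 0–42 | X | | | none: no follow-up |
| Infant distress scale | 1–36 | X | | | none: no follow-up |
| BITSEA | 12–36 | X | X | | possible within its age range |
| Child behaviour checklist | 18+ | | X | X | none: no entry score |

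**Step 2: where the shortage of change data comes from.** Let a be age at entry in months. A BITSEA pair at 12 months needs a ≥ 12 and a + 12 ≤ 36, so a from 12 to 24. With entry age assumed uniform on 0–36, that is 12/36 = 33%. Over other age mixes the share runs from 0% (all enter at 24–36) to 100% (all enter at 12–24). A pair at 24 months needs a = 12 exactly: 0%, or about 4% if baseline falls up to three months after entry. At 36 months every child is at least 36 months old, so the share is 0%. BITSEA is not scheduled at school. The checklist is age-valid for every child at 36 months and at school, but has no entry score. The shortage at the hypothesis time points therefore comes from BITSEA's age ceiling and the checklist's missing entry score.

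**Step 3: would repeating the two entry-only scales help?** Under the same uniform assumption, age-valid pairs would be:

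- SEGC (a + t ≤ 42): 30/36 = 83%, 18/36 = 50% and 6/36 = 17% at 12, 24 and 36 months.
- Distress scale (a ≥ 1 and a + t ≤ 36): 23/36 = 64%, 11/36 = 31% and 0%.

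If all children entered at 24–36 months, the SEGC shares would be 50%, 0% and 0%. At 36 months the yield is small or nil, and school-age children are beyond both ranges.

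**Step 4: can nearly all children have an entry score?** SEGC: the oldest possible baseline age is 36 + 3 = 39 months, inside 0–42, so all can. Distress scale: if taken on the day of entry, 35/36 = 97%; if always taken three months later (ages 3–39), 33/36 = 92%.

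**Step 5: gain from using the entry scores as covariates.** The comparator is an unadjusted follow-up comparison of the checklist. If r is the within-arm correlation of the entry score with the later checklist score, residual variance is multiplied by 1 − r², and 45 per arm is worth 45/(1 − r²):

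| r | Variance reduction | Equivalent n per arm |
|---|---|---|
| 0.1 | 1% | 45/0.99 = 45.5 |
| 0.2 | 4% | 45/0.96 = 46.9 |
| 0.3 | 9% | 45/0.91 = 49.5 |
| 0.4 | 16% | 45/0.84 = 53.6 |
| 0.5 | 25% | 45/0.75 = 60.0 |

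These figures ignore the article's 20% annual attrition and the clustering of siblings.

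**The case against.** The strongest reply is that an Entry-only mark already identifies a baseline measure. The table's title speaks of study measures, and the text says only that they relate to the hypotheses, so the label is a matter of wording. That largely stands: relabelling alone would be a small clarification. It is also fair that covariate choice is often left to an analysis plan that is not shown. Silence on covariates is not the fault here. The article does fix a change rule and t-tests, and the rule cannot be applied to the checklist as scheduled.

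The evidence for 1c is better than a count of instruments suggests. Randomisation makes a follow-up comparison on the checklist unbiased without an entry score, and Data analysis also speaks of a difference in mean outcomes before it specifies changes. DECA, filed under Hypothesis 1b, has a self-control subscale and is collected at Entry, Annual and School.

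A reader might infer that the two entry-only scales are why 1c lacks change data, or that they should be repeated at annual visits. The documents do not support either. Step 2 places the cause elsewhere. Step 3 shows that repeating the SEGC, at the cost of extra visits' burden, would give about 17% valid pairs at 36 months under uniform entry age, and none at school.

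Finally, the correlation is unsourced, and between an infant scale and a checklist about three years later it may be low. That also stands, which is why the range starts at 0.1.

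**Conclusion.** The point holds as a modest, nearly free improvement. The schedule facts are exact: under the change rule the SEGC and the distress scale cannot estimate an EYEP effect, and the checklist cannot follow the rule at all. It would go too far to say that Hypothesis 1c is untestable.

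Adjusting the checklist comparison for entry scores already collected is a better method than the unadjusted test. The gain is a 1% to 25% variance reduction for r between 0.1 and 0.5, or about 45.5 to 60 per arm before attrition and sibling clustering. At the low end it is negligible. For BITSEA, which has its own entry score, the added gain would be smaller. The conclusion assumes that the entry scores are not themselves affected by allocation, which matters because baseline may fall up to three months after entry.

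**What to change.** In Data analysis, state that the arms will be compared on the Child behaviour checklist at follow-up by regression (ANCOVA), adjusting for age and for the age-standardised entry SEGC and/or distress-scale scores, in place of the change-score comparison that this measure cannot support. In Table 1 or its text, describe the SEGC and the distress scale as baseline measures rather than impact outcomes. Mention DECA self-control as related change data for Hypothesis 1c. Choose the entry scale or scales and the age standardisation before outcomes are examined by arm, and note any entry scores taken after attendance began.

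The cost is analysis wording on data already scheduled for collection. No new instrument, visit or repeat of the SEGC is needed.
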